## Abstract

**Background:**

The desire for fertility is the manifestation of yearning for immortality. Infertility and assisted reproductive technology (ART) expose couples to great affective, anxiety, stress, and financial burden. Increasing evidence emphasize the impact of lifestyle on infertility. One of the most crucial factors affecting the fertility process is the nutrition patterns, the amount and quality of physical activities, emotional problems management; modulate stressors, relief from anxiety, and the living conditions of couples. Most ART treatment interventions in Iran are not integrated into lifestyle programs. Therefore, this research will investigate the impact of mixed fertility health-promoting programs in couples who use ARTs.

**Methodology/Design:**

This study entails three steps. The first step includes the systematic review of literature on a health-promoting lifestyle in infertile couples undergoing ARTs, a systematic review of observational studies and interventions in couple’s lifestyle, then, a systematic review of qualitative studies on infertility in couples and their lifestyle, and in the final step couple’s life style literature systematically will evaluate in Iran. In case of failure to obtain the required results from systematic reviews, cross-sectional studies will be carried out to determine the lifestyle of infertile couples receiving ARTs. In the second stage, by holding a panel of experts, an intervention is planned based on the results of the previous stages in order to improve the lifestyle of couples. In the final step, the designed intervention will be administered as a random clinical trial—on ART candidates, in intervention or control groups in one of Iran University of Medical Sciences hospitals. Afterward, the data’s will be evaluated by using standard questionnaires, that include health-promoting lifestyle questionnaire (HPLII), Beck’s depression inventory (BDI), international physical activity questionnaire—short form (IPAQ-SF), and food frequency questionnaire (FFQ). The statistical analysis will be carried out in SPSS software. During the study, subjects meeting the inclusion criteria were randomly selected and randomized into the intervention and control groups. The health-promoting lifestyle training program will be executed for the intervention group while the standard care program is administered to the control group. The content of this program will be obtained from the consensus opinions of the expert panel. The program includes diet recommendations, physical activity, and stress management. Appropriate time, frequency, duration and number of activities will be considered. Communication with subjects will be possible through private meeting special comfort room. Support to the participants will also be through clinical visits social media, SMS and phone calls. Nutritional changes, physical activity amount, anxiety and stress level, abdominal circumference (AC), and body mass index (BMI) will be measured after the completion of the specified time interval. The initial outcome includes examining chemical pregnancy (2 weeks after the transmission) and clinical pregnancy by ultrasound (6 weeks after). The secondary outcome will be live birth rate. Retrieved oocyte and embryo numbers will also be reported.

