### Third stage

In this step, a mixed training program, attained based on the expert panel consensus in each selected health related dimensions, will be held in the form of a clinical trial to determine its effectiveness on retrieved oocytes number, sperm parameters, pregnancy rate, Live birth rate.

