## Sample size and sampling method

The sample size is estimate based on similar studies on the lifestyle of infertile couples [24]. The comparison formula between two ratios will be used at the 95% confidence level The Cronbach’s α of 0.05 and power of 80% will be considered. Finally, 600 couples will be included in the study, of which 150 female and 150 males will be placed in the lifestyle program group and the rest in the control group.

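### Two pregnancy outcomes are primary without ranking, and the single alpha and 80% power are tied to neither

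*Protocol article*

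**What the plan says.** The Methodology/Design part of the abstract sets the outcomes: "The initial outcome includes examining chemical pregnancy (2 weeks after the transmission) and clinical pregnancy by ultrasound (6 weeks after"). The next sentence reads "The secondary outcome will be live birth rate". Set against a secondary outcome, *initial* can only mean primary, so two outcomes hold that status.

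The Third stage objective is to "determine its effectiveness on retrieved oocytes number, sperm parameters, pregnancy rate, Live birth rate". Here pregnancy is one undivided item among four, and none is ranked.

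Under Sample size and sampling method, the basis is given as "The sample size is estimate based on similar studies on the lifestyle of infertile couples [24"]. The method is "The comparison formula between two ratios will be used at the 95% confidence level", and the design values are "The Cronbach’s α of 0.05 and power of 80% will be considered". No outcome is named, and neither of the two proportions is given.

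The Data analysis section assigns chi-square tests and t-tests by type of variable. It attaches no test to either pregnancy outcome.

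**The concern.** A trial with two primary outcomes needs a rule: one decides, either suffices, both are required, or they are tested in order. The choice fixes what the stated alpha and power mean. Without it, a single 5% level and a single 80% describe no identifiable test, and the headline outcome could be chosen after the results are known.

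A reader will probably take the trial to have 80% power for pregnancy at a 5% error rate. Nothing in the article lets the reader confirm that, for either outcome or for the pair. The wrong name for alpha adds to the confusion, because Cronbach's α is a reliability coefficient for questionnaires and not a type I error rate. That slip alone changes no number, since the 95% confidence level stands beside it.

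**Working it through.** **The plan's own figure.** The stated sample size cannot be reproduced or refuted. A two-proportion formula needs a control rate and an intervention rate, and neither is given. Everything below therefore uses assumed pregnancy rates.

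**Step 1: correlation of the two tests.** Clinical pregnancy is treated as nested within chemical pregnancy. With chemical rate p1 and clinical rate p2, the correlation of the two outcomes, and so of the two test statistics under no effect, is

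r = √[ p2(1 − p1) / ( p1(1 − p2) ) ].

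Assumed: p1 of 35% to 40%, of which 70% to 90% becomes clinical. The extremes are:

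- p1 = 0.40, p2 = 0.7 × 0.40 = 0.28: r = √(0.168 / 0.288) = 0.764
- p1 = 0.35, p2 = 0.9 × 0.35 = 0.315: r = √(0.20475 / 0.23975) = 0.924

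**Step 2: error rate if either outcome suffices.** Each test is two-sided at 0.05, and the error rate is 1 − P(|Z1| < 1.96 and |Z2| < 1.96) under a bivariate normal with correlation r.

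- r = 0.764: 8.0%
- r = 0.924: 6.8%
- Independent tests, as an upper reference: 1 − 0.95² = 9.75%

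**Step 3: power if both must succeed.** Alpha stays at or below 0.05. If each test has 80% power, each statistic has mean 1.96 + 0.842, and the joint power is P(both exceed 1.96) = Φ₂(0.842, 0.842; r).

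- r = 0.764: 72%
- r = 0.924: 76%
- Independent tests, as a lower reference: 0.8 × 0.8 = 64%

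**Step 4: what 80% power means for one pregnancy outcome.** With n couples per arm, rates a and b, and mean rate m = (a + b)/2,

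power = Φ{ [ |a − b|√n − 1.96√(2m(1 − m)) ] / √( a(1 − a) + b(1 − b) ) }.

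The arm size is itself uncertain. The sample size section says 600 couples, which is 300 per arm at 1:1, but places 150 women and 150 men in the programme group, which is 150 couples. The randomisation section builds 75 blocks of 4 for 300 people. Read as individuals, that is 150 couples, or 75 per arm.

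| Couples per arm | Detectable gain at 80% power, control 20% / 30% / 40% | Power for 30% vs 40% |
|---|---|---|
| 300 | 9.9 / 10.9 / 11.4 points | 73% |
| 150 | 14.3 / 15.6 / 16.1 points | 44% |
| 75 | 20.9 / 22.3 / 22.7 points | 25% |

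Example at 150 per arm, 30% vs 40%: [0.10 × 12.247 − 1.96 × 0.6745] / 0.6708 = −0.145, and Φ(−0.145) = 0.44. The same formula needs 356 couples per arm for 80% power in that comparison.

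**Step 5: cost of splitting alpha instead.** For an assumed 30% vs 45%, testing at 0.05 needs 163 couples per arm and testing at 0.025 needs 197. The ratio is 197/163 = 1.21, about 21% more couples.

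**The case against.** Four points can fairly be made for the plan.

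*The success rule may be written elsewhere.* A multiplicity procedure is often left to an analysis plan, and a journal article condenses the full protocol. That is why the absence of such a procedure is not the point here. Which outcome is primary is a protocol decision that the article does state, and it states two without order.

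*No either-or rule is set.* A reader might infer that the false-positive rate exceeds 5% as a matter of fact. The documents do not support that. The inflation arises only if either outcome may be claimed. Requiring both, or testing in a fixed order, keeps alpha at 5%. Even under the either-or reading it is moderate, because the two outcomes overlap heavily. This objection stands, and the error rate is given here only as conditional.

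*The sizing may well concern pregnancy.* A reader might infer that the 80% power comes from lifestyle studies and so does not refer to pregnancy. The text says that the sample size rests on those studies, while alpha and power are stated separately as design values. The cited source is not available here, so whether it contains pregnancy rates is unknown. A two-proportion formula also fits a binary outcome such as pregnancy. This objection stands too. What can be said is that the outcome behind the 80% is not identified.

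*Clinical pregnancy need not be the choice.* A co-primary rule or a fixed order would also resolve the ambiguity. That is correct, and the fix allows for an order.

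**Conclusion.** The point holds in limited form. The article names two unranked primary outcomes and gives one alpha, under the wrong name, and one power, both tied to neither. The consequence depends on the rule eventually applied. If either outcome suffices, the false-positive rate is about 6.8% to 8.0% in place of 5%. If both are required, joint power is about 72% to 76% when each test has 80%.

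These figures rest on assumed rates (chemical pregnancy 35% to 40%, of which 70% to 90% becomes clinical), on nesting of the two outcomes and on a normal approximation.

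The power figures in the table should not be read as the trial's actual power. They rest on assumed control rates, and a reader who takes 150 couples per arm as settled would be choosing one of three readings of conflicting text.

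**What to change.** 1. Name one deciding primary outcome, for example clinical pregnancy per randomised couple, with chemical pregnancy as secondary beside live birth. Alternatively, keep both and state a fixed testing order.
2. Replace Cronbach's α of 0.05 with a two-sided type I error of 0.05.
3. Reconcile the number of couples between the sample size and randomisation sections. Then restate the 80% power as the detectable difference in the chosen outcome, with the assumed control rate and its source.

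These are changes of wording and add no couples, whereas splitting alpha would need about 21% more in the example above. They should be made before outcome data are seen. The price is that chemical pregnancy loses primary status, or is tested second, and that the detectable effect may look less favourable than readers now suppose.

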
**Discussion:**

Health-promoting lifestyle programs are essential in assisted reproductive technologies to improve pregnancy results and live birth. These programs in association with in-vitro fertilization (IVF) influence the outcome of fertilization. In addition, enhancing parental health leads to healthy pregnancy outcome. Despite the frequency of lifestyle risk factors, employing proper methods helps reduce anxiety and stress, modify dietary patterns, and perform qualitatively and quantitatively balanced physical activities. In addition, having coping skills and mental health management methods, in nowadays modern world challenges seems crucial and effective in solving fertility problems and reducing them before pregnancy.

## Background

Amongst all steps in the lifecycle of a living creature, the highest evolutionary pressure is exerted on the process of fertility [1]. The most recent reports indicate a decrease in the live birth rate [2]. Considering the rising rate of infertility [3] and the need to use ART, lifestyle factors are more emphasized. The WHO defined infertility as a disease in the male or female reproductive system, which failed to achieve pregnancy after 12 months of unprotected sexual intercourse. In total, 186 million people and 48 million couples are infertile worldwide [4]. Infertility has destructive social and health consequences including social stigma, economic problems, and poor physical and mental well-being [5]. Following a meta-analysis report, the lifetime prevalence of infertility amounted to (3.3–21.3%) in the Eastern Mediterranean Region, 7% in England, and 30% in African countries [4, 6]. The population problem is a fundamental issue concerning policy-making and future planning. Based on the 2019–2020 censuses, the total fertility rate in Iran decreased to 1.2 children per woman. Taking into account the current fertility process, the population growth will approach zero between 2036 and 2041 [7]. ART comprises all methods in which oocytes, sperms, and embryos are directly manipulated outside the body in in-vitro. The first and most common form of ART is in vitro fertilization (IVF) [8]. The effects of lifestyle on infertility shown in the accumulated data from various studies suggest that such factors as smoking, depression, and anxiety can contribute to infertility [4]. Furthermore, mounting evidence indicated that obesity, an imbalanced diet, and a lack of physical activities play a crucial role in infertility causes [9]. Recent studies pointed out that inflammation in the body can cause damage to Germ cells. Following a diet rich in antioxidants, flavonoid resources, and unsaturated fatty acids, and decreasing the consumption of red meat, particularly processed meats, are effective in reducing inflammation. Sticking to a proper diet before pregnancy is an effective key solution [10]. Food-based dietary guidelines (FBDG) recommend reducing the sugar and saturated fat intake and increasing the use of unsaturated fat, seeds, whole grains, fruits, and fish [11]. The Mediterranean diet (MD) is one of the healthiest and most beneficial diets in the world. Food intake pattern in this diet includes large amounts of pulses, seeds, whole grains, fruits and vegetables, median intake of fish and wine, and low intake of dairy products and red meat. Fat intake resources are olive and olive oil. This diet is a rich source of unsaturated fats, fibers, antioxidants, and the minimum amount of saturated fats [12]. Vojokovic conducted a study in the Netherlands on the relationship between dietary styles and infertility and identified two dietary patterns. The first pattern (health conscious–low processed) emphasizes the high intake of fruits, vegetables, whole grains, and seeds and the low intake of processed foods, such as Mayonnaise, snacks, and meat products [13]. Noori’s study suggested that dairy consumption affects sperm parameters, whereas the consumption of saturated fats and calcium resulted in poor-quality sperm. On the other hand, the consumption of high amounts of folate and selenium, plus low consumption of cholesterol has a positive impact on the improvement of sperm parameters [14]. In their study, Xiao Cheng indicated that healthy diet adjuvant therapy, Mediterranean diet (MD), Ketogenic diet (KD), and dietary approaches to stop hypertension (DASH) were effective on fertility results [15]. Results of some studies demonstrated the impact of a sedentary lifestyle, and as a result, low health-related quality of life (HRQoL) on infertile people. Furthermore, high BMI and the increase in anxiety and stress affect HRQoL [16]. Even though exercise is regarded as a general improving factor, excessive exercise has an unpleasant and inhibitor impact on the hypothalamic–pituitary–adrenal axis (HTP axis). In the study by Minas, exercise reduced oxidative stress and improved chronic inflammation by increasing antioxidant defense in the testes. In addition, it decreased obesity, diabetes, and infertility rate [17]. The effective factors on the well-being and health of women with primary infertility were investigated in India and factors, such as psychological problems, duration of infertility, insufficient physical activity, education level, sleeping pattern, and family structure were shown to be crucially important in infertility [18]. The study by Palomba on 216 women under the treatment by IVF/ICSI revealed that regular physical activity before fertilization procedure improves fertility outcomes in infertile obese women [19]. Gaskin in the study of environment and fertility health (EARTH) examined the physical activity in 427 women under IVF treatment. The results showed that 2.8 h of average or severe physical activity per week has no significant impact on embryo implantation, clinical pregnancy, and live birth. However, women performing activities, such as aerobics, skiing, and boating had a higher rate of live birth [20]. In addition to the impact of exercise and physical activity on general health and fertility, it is quite clear that the type of food and diet styles is amongst the crucially important pillars of a healthy life, mental and psychological health, and psychological issues. Diagnosis of infertility is followed by comprehensive anxiety and stress and causes consequences, such as depression, unhappiness, guilty feeling, low self-esteem, destroyed self-confidence and inability to overcome obstacles and problems [21]. Research reported the anxiety rate caused by infertility amounts to approximately 75.9% in women and 60.6% in men. This high anxiety level and stress pressure affects couples’ fertility health [22]. Regardless of the impact of infertility on the stress and anxiety rate, IVF/ICSI procedures can cause stress and anxiety. Supporting couples in this step and providing them with the required stress and anxiety management training helps improve the quality of their life and increase the possibility of achieving their valuable wish’s goal [23]. Numerous factors affect lifestyle. Health-promoting lifestyle includes the following six dimensions: diet, exercise, stress management, health responsibility, interpersonal relationships, and spiritual growth leading to self-actualization. Lifestyle refers to all behaviors controlled by the individual, or behaviors that affect personal health risk factors [24]. A comprehensive approach suggests that health-protective behaviors (HPB) (risk reduction and prevention) and health-promoting behaviors can be regarded as two supplementary components of a healthy lifestyle. These behaviors, improve the health, self-actualization, and psychological maturity ‏of individuals. The European Society of Human Reproduction and Embryology (ESHRE) guideline argues that multipurpose programs in various fields are crucial to meet cognitive, communicative, and mental-psychological needs, as well as consultation concerning lifestyle [25]. Doomar conducted a study on 12,800 infertile women and found that IVF candidates have habits, such as smoking, drinking coffee and alcohol, having a sedentary lifestyle, and the use of recreational or unauthorized drugs [26]. Studies in Iran showed the prevalence of psychological disorders including depression, hypochondriasis, and paranoia among infertile couples [27], and these groups exhibited a high tendency toward unhealthy and Western nutrition [28]. Furthermore, the increase in exercise in women with IVF pregnancy was associated with a significant decrease in gestational diabetes and pre-eclampsia [29]. In the study by Baheiraei on the lifestyle of infertile couples, negligence towards a healthy lifestyle, particularly among men, indicates that this group needs appropriate health protection training programs before carrying out infertility treatments, as well as during and after IVF interventions [30]. A tailored literature-based program includes nutrition, physical activity, and exercise, together with stress reduction in the course of IVF/ICSI interventions. Similar integrated studies that include a combination of various health dimensions have rarely been conducted in Iran. The necessity of these programs in fertility clinics before beginning any medical treatment or procedure concerning the fertilization procedures is sensed and their absence can affect fertilization outcomes. It is hoped that this study can improve fertilization outcomes by promoting couples’ lifestyles.

## Aims of study

The main aim of the study in the first stage is to design a lifestyle intervention program in infertile couples receiving assisted reproductive technologies (ART). Then studies on the lifestyle of couples undergoing IVF/ICSI treatment will be identified and investigated. Choosing a suitable and beneficial program to promote health in men and women will be examined. After that, lifestyle risk factors (e.g., the lack of physical activity, unhealthy diet, consumption of fast foods and processed foods, weight gain and obesity, consumption of alcohol and coffee, smoking, use of other stimulants and narcotic drugs), psychological pressure complications (e.g., depression, stress, and anxiety), the lack of adequate alleviating training to manage stress and anxiety, sleep disorders, insomnia and sleep hygiene in couples will be investigated and studied. In the next step, an intervention will be executed and its effectiveness will be determined (Fig. 1).

**Fig. 1 Fig1:**
[figure not shown]
Study diagram

## Specific objectives of study

### First stage

Identifying the lifestyle of infertile couples undergoing ARTs in the observational studies through a systematic review.Identifying the lifestyle of infertile couples undergoing ARTs in the interventional studies through a systematic review.Identifying the lifestyle of infertile couples undergoing ARTs in the qualitative studies through a systematic review.Determining the impact of lifestyle-promoting interventions, concerning diet, on infertile couples undergoing ARTs using available studies.Determining the impact of lifestyle-promoting interventions, concerning physical activity, on infertile couples undergoing ARTs using available studies.Determining the impact of lifestyle-promoting interventions, concerning stress management, on infertile couples undergoing ARTs using available studies.

### Second stage (experts’ panel)

A survey will be conducted on expert’s advices and a lifestyle-promoting intervention for infertile couples undergoing ARTs will be designed by establishing an expert panel.

### Third stage

In this step, a mixed training program, attained based on the expert panel consensus in each selected health related dimensions, will be held in the form of a clinical trial to determine its effectiveness on retrieved oocytes number, sperm parameters, pregnancy rate, Live birth rate.

## Design and methodology

This research is conducted based on Standard Protocol Items (SPIRIT) [31].

The study entails three stages that start with a systematic literature review. A cross-sectional study will be carried out if the desired results are not achieved in the first stage. An expert panel will be held qualitatively to survey experts in various lifestyle fields. A consensus of opinions will be obtained after collecting the opinions of experts and professors in lifestyle dimensions. A tailored training program, developed based on the results of the previous step, will be designed. After selecting a suitable lifestyle training program for the couples undergoing ART, the impact of the intervention will be examined via clinical trial. The obtained data will be analyzed by SPSS software.

